### Primary outcome

The primary study outcome is the difference in proportion of patients scoring ≥3 points on at least one of the BPRS questions 5 days postoperatively – or earlier at discharge – between the hydrocortisone and placebo group. A better outcome on the BPRS in the hydrocortisone group would be considered a positive result, which would indicate that addition of hydrocortisone to dexamethasone is beneficial to reduce neuropsychiatric adverse effects of dexamethasone.

### Secondary outcomes

Secondary outcomes are neuropsychiatric symptoms, quality of sleep, HRQoL, and neurocognitive functioning 5 days postoperatively – or earlier at discharge –, 2 weeks, 5 to 8 weeks, and 3 months postoperatively. Furthermore, neuropsychiatric history, SAEs, prescribed (psychiatric) medication and referrals or evaluations of psychiatrist/psychologist will be collected. In addition, the laboratory measurements are considered secondary outcomes.

### Sample size

The sample size calculation is based on the results of a pilot study in which we tested the BPRS in our study population. We determined postoperative BPRS scores to evaluate the presence of psychiatric symptoms in brain tumour patients who underwent surgery and were treated with dexamethasone. We interviewed 18 patients on the day of hospital discharge. According to the BPRS scores in this group we considered a score of ≥3 on at least one of the BPRS items as clinically relevant for patients. We found that 7 out of 18 patients (≈40%) scored at least ≥3 on one of the BPRS items. Based on expert clinical judgement a 50% reduction in the patients with a score ≥3 is perceived as relevant. This equals an absolute difference of 20%. If we consider an α=0.05 and a power of 80%, and we take the 20% absolute difference between the two treatment arms, a sample size of 82 patients in each group would be needed. Based on an expected drop-out rate of ≈10%, 90 patients in each treatment arm (in total 180 patients) will be considered as a satisfactory sample size.

### Planned statistical analyses

This study is a randomised controlled trial. All data will be analysed on an intention-to-treat basis.

#### BPRS

The primary study parameter is the proportion of patients scoring ≥3 points on at least one of the BPRS questions 5 days postoperatively – or earlier at discharge. The difference in these proportions between the placebo group and the hydrocortisone group will be calculated and statistically compared with the Chi-Square test. Any difference with a p<0.05 will be considered significant.

As secondary analyses, both treatment arms will be compared over time using analysis of repeated measures, generalised estimating equation (GEE) for the dichotomous outcomes as described in the primary outcome and the mixed linear model for the BPRS as continuous outcome. Additionally, we will look at the differences between the treatment arms on the separate items of the BRPS.

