### Study outline

A timeline of the study is shown in figure 3. Eligible patients are approached in an outpatient setting by specialised nurses in consultation with the treating neurosurgeon. The study is explained and written information is provided (online supplemental files S2,3). After written informed consent by the coordinating investigator or principle investigators, patient characteristics (age, gender, educational level, medical background, medication use, tumour type and tumour location) are recorded. The informed consent form includes consent for collection for blood sample and residual tumour tissue. Before start of intervention, a baseline study visit is planned that includes a structured psychiatric interview, different self-report questionnaires, and neurocognitive tests. A selection of the questionnaires can be filled out online via the web-based database programme Castor Electronic Data Capture (EDC; Castor, Amsterdam, The Netherlands). The intervention starts on the day of hospital admission, concurrent with the dexamethasone treatment 1 day prior to planned surgery. 5 days postoperatively – or earlier at discharge – a structured psychiatric interview and neurocognitive screening are conducted, and questionnaires are filled out. The study medication is provided to the patients according to clinical care and is continued as long as dexamethasone is prescribed. A follow-up visit is planned 5 to 8 weeks postoperatively coinciding with the regular care assessment, at which a structured psychiatric interview and neurocognitive tests are performed and different questionnaires are filled out. Study visits take place at the medical centre of treatment. 2 weeks and 3 months postoperatively questionnaires can be filled out online via Castor EDC. Study duration from start of intervention until completion of the last questionnaires is 3 months. The study schedule is shown in table 1. In case the baseline study visit is planned the day before surgery, no neurocognitive tests will be performed – instead a neurocognitive screening may be performed – and presentation of the questionnaires is depend on the patients’ psychological and physical condition. To improve adherence the follow-up visits are coinciding with the regular care assessments.

10.1136/bmjopen-2021-054405.supp2Supplementary data

10.1136/bmjopen-2021-054405.supp3Supplementary data

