### Allocation, randomisation and blinding

Randomisation is controlled by the Clinical Pharmacy and Toxicology department of LUMC using block randomisation in a 1:1 ratio stratified for each medical centre participating in the study, and for tumour type (glioma or meningioma) with block size of 10. New study participants are assigned to a randomisation number by the coordinating investigator. The coordinating investigator will contact the local pharmacy about the patient and its randomisation number. The local pharmacy assigns the randomisation number to a medication number and then the pharmacists know the treatment allocation. The randomisation list is stored at the department and will not be disclosed until all participants have completed the trial. Only in case of emergency and the knowledge of the assigned treatment is required, the randomisation code can be broken. The study is blinded for everyone involved, except the pharmacy who allocates participants to treatment. In addition, hydrocortisone and placebo pills are identical in terms of appearance and taste ensuring blinding.

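### The primary Chi-Square test is valid but uses neither baseline BPRS nor the randomisation strata, forgoing precision that costs nothing to recover

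*Protocol article*

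**What the plan says.** The Primary outcome section defines the endpoint as a post-operative status: "The primary study outcome is the difference in proportion of patients scoring ≥3 points on at least one of the BPRS questions", assessed five days after surgery or at discharge if that comes sooner. Under Planned statistical analyses, BPRS, the primary test is named: "The difference in these proportions between the placebo group and the hydrocortisone group will be calculated and statistically compared with the Chi-Square test", with p<0.05 decisive.

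Two sources of baseline information are available.

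- **Strata.** The Allocation section describes block randomisation "stratified for each medical centre participating in the study, and for tumour type (glioma or meningioma) with block size of 10". Four centres take part, so there are 4 × 2 = 8 strata.
- **Baseline BPRS.** The Study outline says: "Before start of intervention, a baseline study visit is planned that includes a structured psychiatric interview". Table 1 marks the BPRS at baseline and admission without the parentheses it puts around some other instruments at admission, such as the HADS.

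Baseline data enter elsewhere only. The repeated-measures models for the BPRS (GEE and mixed model) are secondary, and regression on baseline predictors is explanatory.

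**The concern.** The Study design section itself lists underlying pathology and psychiatric history among the factors that can influence the main outcome. A pre-treatment score on the same instrument is a natural candidate for a prognostic covariate, and tumour type was thought important enough to stratify on. A primary test that ignores both leaves explainable variation in the comparison.

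What is at stake is power. The design has no reserve: 90 per arm with 10% loss leaves 81 per arm, one below the 82 that the sample size section requires. A modest gain in precision would help if the true effect or the retention falls slightly short of plan.

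**Working it through.** **Inputs from the article (Sample size section).** "If we consider an α=0.05 and a power of 80"%; control rate from the pilot, "We found that 7 out of 18 patients (≈40%) scored at least ≥3 on one of the BPRS items"; halving this rate gives 40% versus 20%, of which the article says "This equals an absolute difference of 20"%; result, "a sample size of 82 patients in each group would be needed". Sidedness is not stated; two-sided reproduces the figure.

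**Step 1: reproduce the stated sample size.** Two proportions, pooled variance under the null, no continuity correction, with p̄ = 0.30:

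n = [1.960·√(2·0.30·0.70) + 0.8416·√(0.40·0.60 + 0.20·0.80)]² / 0.20²
= [1.2702 + 0.5323]² / 0.04 = 3.249 / 0.04 = 81.2, rounded up to 82 per arm.

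This matches exactly.

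**Step 2: power of the unadjusted test.** Power = Φ[(0.20·√n − 1.2702) / 0.6325].

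- n = 82: Φ(0.855) = 80.4%.
- n = 90 × 0.90 = 81: Φ(0.838) = 79.9%.

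The stated 80% is therefore right for the stated test.

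**Step 3: power with adjustment.** The article gives neither the prevalence of baseline symptoms nor their association with the outcome, so both are assumed. In both simulations below, the marginal rates are held at 40% and 20%.

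*Simulation A*: 164 patients, 8 strata, blocks of 10, 3,000 trials per setting. Baseline is binary (any item ≥3) with 25% prevalence (30% in the no-association row). The adjusted test is a logistic likelihood-ratio test with centre, tumour type and baseline BPRS. CMH denotes the Cochran-Mantel-Haenszel test over the eight strata.

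| Baseline odds ratio | Stratum SD (logit) | Chi-Square | CMH, strata only | Adjusted, with baseline BPRS |
|---|---|---|---|---|
| 1 (none) | 0 | 81.1% | 81.0% | 82.2% |
| 3 | 0.3 | 80.8% | 81.0% | 84.1% |
| 5 | 0.3 | 81.1% | 80.9% | 85.8% |
| 5 | 0.6 | 81.3% | 82.5% | 86.8% |
| 10 | 0.5 | 80.2% | 80.5% | 89.6% |

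Null rejection rates over the same settings were 4.4 to 6.1% for the Chi-Square test and 5.3 to 6.5% for the likelihood-ratio test. About 1 point of the adjusted gain therefore reflects a slightly liberal test.

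*Simulation B*: 162 patients, 8 strata, 4,000 trials per setting (6,000 under the null). Baseline and outcome are linked by a latent correlation. The adjusted method is a risk difference with robust variance.

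| Latent correlation | Chi-Square | Adjusted |
|---|---|---|
| 0.3 | about 81% | about 82% |
| 0.5 | about 81% | about 86% |
| 0.6 | about 81% | about 89% |
| 0.7 | about 81% | about 90% |

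Null rejection was 4.3% unadjusted and 4.8% adjusted, so the gain here does not come from an inflated test.

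**Step 4: where the gain comes from.** In simulation A the strata alone change power by between −0.2 and +1.2 points. Adding baseline BPRS brings the total gain over the Chi-Square test to 3.3 points (84.1 − 80.8) at an odds ratio of 3 and 9.4 points (89.6 − 80.2) at an odds ratio of 10. With no prognostic value, power is not reduced (82.2% against 81.1%).

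**Step 5: can the model be supported?** Expected events are 81 × 0.40 + 81 × 0.20 = 48.6. Main effects need 1 (treatment) + 1 (baseline) + 3 (centre) + 1 (tumour type) = 6 coefficients, about 8 events for each.

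**The case against.** The strongest reply is that nothing here is wrong. Randomisation makes the unadjusted test valid, the sample size was computed for that test, and the pilot, target effect, endpoint and test all refer to the same post-operative proportion. The size of the gain is assumed, and the lower end of the range is about 1 point. Adjusted supportive analyses may also sit in the statistical plan, which is to be finalised before analysis. All of this stands, and it makes the point an improvement and not a correction. It does not remove the point, because the article fixes the primary test itself and names no covariate.

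A reader might infer three stronger claims that the document does not support.

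- **That the Chi-Square test makes pre-existing symptoms count as treatment failures.** They count because the endpoint is an absolute post-operative status. An adjusted model keeps that endpoint and reclassifies nobody.
- **That the treatment contrast is diluted by a calculable amount.** This needs the share of events that pre-date treatment and cannot respond to it. The article gives no such share, and the detailed eligibility figure is not shown. Symptoms at baseline may also already be due to dexamethasone: the Eligibility criteria section reports that the exclusion for more than one day of pre-operative dexamethasone was dropped.
- **That ignoring the strata makes standard errors materially too wide.** The simulated null rates of the Chi-Square test lie on both sides of 5%, and the strata alone add about 0 to 1 point of power.

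**Conclusion.** The point holds as a free gain in efficiency of uncertain size. The primary test is valid, and the stated 82 per arm reproduces at 80.4% power. Adjustment for baseline BPRS, centre and tumour type would raise power from about 80 to 81% to about 82 to 90%. The range depends on a latent correlation of 0.3 to 0.7 or a baseline odds ratio of 3 to 10, on the assumed baseline prevalence and stratum spread, and on the planned 40% versus 20%. Baseline BPRS supplies nearly all of it. If baseline BPRS proves unrelated to the outcome, little is lost.

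**What to change.** Before unblinding, make the primary comparison a logistic regression with treatment, baseline BPRS, centre and tumour type (main effects, strata as randomised).

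- **Baseline term.** Fix its form in advance: either the total score or the indicator for any item ≥3.
- **Reporting.** Give a standardised risk difference with 95% CI and p-value, using a robust variance. This keeps the article's target, a difference in proportions. The model's odds ratio should not be the headline: in simulation A the same 40% versus 20% corresponded to conditional odds ratios from 0.38 down to 0.28 as the prognostic strength of baseline rose.
- **Sensitivity analysis.** Keep the Chi-Square test.
- **Optional supportive analysis.** Count items ≥3 after surgery that were <3 at baseline. State the caveat that, with longer pre-operative dexamethasone now allowed, baseline symptoms may already be dexamethasone-related, so this endpoint could discard real benefit.

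The cost is wording in the protocol and statistical plan. The article reports that recruitment is ongoing and that no interim analysis is planned, so on its account the change can be made while blinded, with no new data and no extra patients.

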#### Mini-screen, HADS, PANAS, ASRM, NPI-Q, DOS, LSEQ and HRQoL

Both treatment arms will be compared over time using analysis of repeated measures, GEE when outcome is dichotomous and mixed linear models for continuous outcomes.

Explanatory univariable and multivariable regression analysis will be used to identify (baseline) predictors of treatment response. Sensitivity analysis will be performed using multiple imputation to handle missing data. Any difference with a p<0.05 will be considered significant. A better outcome on the different scales in the hydrocortisone group would be considered a positive result.

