#### Subgroup analyses

Subgroup analyses will be performed to explore differences in our primary and secondary parameters for type of tumour, gender, age and dosage of dexamethasone.

As the study remains blinded until completion, no interim analyses are planned. In addition, the statistical plan will be finalised before starting the analyses.

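### The regression for predictors of treatment response includes a univariable step that can only find prognostic factors, and no treatment-by-factor interaction is named for the multivariable step

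*Protocol article*

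**What the plan says.** The sentence stands in the protocol article under Planned statistical analyses, in the part on the secondary scales (Mini-screen to HRQoL): "Explanatory univariable and multivariable regression analysis will be used to identify (baseline) predictors of treatment response". The same paragraph sets the threshold: "Any difference with a p<0.05 will be considered significant". It does not define treatment response, list model terms, or say whether one or both arms enter the regression.

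The Subgroup analyses section adds: "Subgroup analyses will be performed to explore differences in our primary and secondary parameters for type of tumour, gender, age and dosage of dexamethasone". It names no test. It also says that "the statistical plan will be finalised before starting the analyses".

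No section of the article mentions a treatment-by-factor interaction, and none rules one out.

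**The concern.** The sentence names both a target and a tool, and one part of the tool cannot reach the target. The trial is parallel-group and placebo-controlled, so nobody's outcome is seen under both treatments. The Discussion itself counts the lack of a cross-over design as a drawback. Whether a factor predicts response therefore means whether the difference between hydrocortisone and placebo changes with that factor. A regression on the factor alone answers a different question: who does worse, whatever the treatment.

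Prognostic factors are to be expected here. The Study design section lists underlying pathology, tumour location, extent of surgery and psychiatric history as possible influences on the main outcome. At p<0.05, such factors could appear under a label that implies they identify who benefits from hydrocortisone.

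The brackets around the word baseline add a smaller uncertainty, because they leave it open whether only baseline factors are meant. Dexamethasone dosage, one of the subgroup factors, shows why this matters. The adverse-event section expects dexamethasone to be increased, or its reduction scheme extended, for oedema in some patients. Total dosage can therefore be a post-randomisation variable.

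**Working it through.** **Step 1: the plan's own figure.** Inputs from the Sample size section are "We found that 7 out of 18 patients (≈40%) scored at least ≥3 on one of the BPRS items" (7/18 = 38.9%, taken as 40%), "This equals an absolute difference of 20" points (so 40% against 20%), α = 0.05 (taken as two-sided) and 80% power.

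n per arm = [1.96·√(2·0.30·0.70) + 0.842·√(0.40·0.60 + 0.20·0.80)]² / 0.20² = 81.2, rounded up to 82.

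This agrees with "a sample size of 82 patients in each group would be needed". Inflating for 10% drop-out gives 82/0.9 = 91.1, or 92. The stated 90 leaves 81 evaluable per arm and 79.9% power. The sample size holds and does not bear on this point.

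**Step 2: what a factor-only model estimates.** The article gives no factor prevalence or prognostic odds ratio, so these are assumptions. Take a binary baseline factor with 50% prevalence and prognostic odds ratio 3, with the same treatment odds ratio (0.35) in both strata and overall event rates of 40% and 20%. Solving the logistic model (intercept −0.986, treatment −1.040, factor ln 3) gives:

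| | Factor absent | Factor present |
|---|---|---|
| Placebo | 27.2% | 52.8% |
| Hydrocortisone | 11.7% | 28.4% |
| Arms pooled | 19.4% | 40.6% |

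The univariable model compares 19.4% with 40.6%. That 21-point gap is wholly prognostic, because the treatment odds ratio does not differ between the columns.

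**Step 3: how often each model flags such a factor at p<0.05.** Logistic simulation with 82 per arm and 3,000 trials per scenario:

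| Model | OR 1 | OR 2 | OR 3 | OR 4 |
|---|---|---|---|---|
| Factor alone, arms pooled | 4% | 48% | 84% | 96% |
| Factor + treatment, no product | 5% | 49% | 86% | 97% |
| Factor alone, hydrocortisone arm only | 4% | 20% | 45% | 62% |
| Treatment-by-factor interaction | 5% | 5% | 4% | 3% |

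A second set-up used 81 per arm, 30% prevalence, a treatment odds ratio of (0.20/0.80)/(0.40/0.60) = 0.375 and 1,500 trials per scenario. At odds ratios 2, 3 and 4, the univariable model flagged the factor in 43%, 80% and 96% of trials, and the interaction test in 5.8%, 3.7% and 5.0%.

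**Step 4: power of the right test.** Take 164 evaluable patients and a 50/50 factor, so 41 per cell, with a normal approximation on the risk-difference scale and 40%/20% variances throughout.

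SE = √[2·(0.24 + 0.16)/41] = √0.0195 = 0.140.

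- 20-point difference in effect: Φ(0.20/0.140 − 1.96) = about 30%.
- 40-point difference in effect: Φ(0.40/0.140 − 1.96) = about 82%.

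**A note on scale.** In Step 2 the odds ratio is constant but the risk differences are not: 27.2 − 11.7 = 15.5 points against 52.8 − 28.4 = 24.4 points. An interaction exists or not only on a given scale, so the scale has to be stated.

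**The case against.** The strongest reply is that the article condenses a fuller plan. It gives no model terms, and the statistical plan was still to be finalised. The terms of an exploratory secondary regression are the kind of detail an article leaves out, and univariable may mean only that candidates are screened one at a time before a fuller model. For the multivariable step this stands: a reader might infer that interactions are excluded, but the article is merely silent. The reply does not rescue the univariable step. That method is named, it cannot contain an interaction by construction, and its results are tied to treatment response.

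Three other strong readings are tempting and not supported.

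- *The subgroup section repeats the fault.* A reader might take it to compare outcome levels between subgroups, since the BPRS section defines the primary parameter as a proportion. But the Primary outcome section defines the outcome as a difference between arms, and the usual meaning of a subgroup analysis in a randomised trial is the treatment contrast within subgroups. The sentence is ambiguous, not wrong.
- *The resulting list will be used to select patients for hydrocortisone.* No section plans this. The Discussion speaks of a possible option for the patient group as a whole.
- *Many patients never have symptoms, so response is undefined for them.* The limitations list says only that some patients do not experience adverse effects.

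The simulations are also conditional. Prevalence and odds ratios are assumed, and the event rate comes from the BPRS pilot, whereas many scales under this heading may be analysed as continuous. They show the mechanism, not what this trial will report. Low interaction power is a fair point too, but it argues for modest claims, not for a test of a different question.

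**Conclusion.** The point holds in a limited form. The univariable step cannot identify predictors of treatment response, and no interaction is named for the multivariable step. The analysis as written therefore risks reporting prognostic factors as predictors of response to hydrocortisone.

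Illustratively, across both set-ups, a purely prognostic factor with an odds ratio of 2 to 4 is flagged in about 43% to 97% of trials when the arms are pooled without an interaction. Within the hydrocortisone arm alone the figure is 20% to 62%, and with an interaction test it is about 3% to 6%. These figures rest on assumed prevalences of 30% or 50%, a binary outcome at 40% against 20%, and a constant treatment odds ratio.

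Mislabelling is a risk, not a certainty: it depends on the model finally fitted and on how it is interpreted. The primary chi-square test, the between-arm comparisons on the secondary scales and the sample size are untouched. This is a minor-to-moderate correction to a secondary exploratory analysis.

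**What to change.** Replace the sentence with wording such as: *Effect modification will be explored, for baseline factors only, by fitting treatment, factor and treatment-by-factor terms in the outcome model. The interaction estimate and its 95% CI will be reported, on a stated scale, as hypothesis-generating.* Add that power is low.

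Use the same interaction model for the subgroup analyses and say that they concern the between-arm effect. For dexamethasone dosage, define the subgroup by a value fixed before randomisation, such as the planned scheme, or report it separately as not a baseline factor.

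If univariable or main-effects results are kept, call them prognostic factors.

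The cost is a few lines in the statistical plan before it is finalised. No extra patients or data are needed. The price is wide intervals and fewer claimed predictors.
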